**Figure 1 F1:**
[figure not shown]
Example T1-weighted MRI images, and three-point Dixon MRI-obtained quantitative fat-fraction maps, from a healthy volunteer **(top images)**, and a person with CMT1A **(bottom images)**.

Therefore, the goal of the Accelerate Clinical Trials in CMT study (ACT-CMT) is to validate COAs and biomarkers for use in clinical trials involving adults with CMT1A. Specifically, we will evaluate the reliability, examine the construct and convergent validity, and document responsiveness to disease progression of the CMT-FOM. Similarly, using quantitative three-point Dixon MRI, we will examine the reliability, convergent validity and responsiveness to change of IMFA as measured by muscle fat fraction (FF) to validated it as a biomarker of calf-level muscle involvement, and last, we will assess the reliability, construct and convergent validity and ability to detect change of RCM of MC density to validate it as a sensory disease progression biomarker for use in multi-site CMT1A trials. We also aim to increase the efficiency of trial design by using data to refine eligibility criteria.

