## Sample Size

We are recruiting 215 individuals with CMT1A to participate in this study. This baseline sample will provide >90% power to detect correlations between the CMT-FOM and existing COAs and PROs as small as 0.22. We anticipate that 180 participants will complete the assessments at the 30-month visit (accounting for up to a 15% dropout). This sample size will provide >80% power to detect significance of a mean change of 0.21 standard deviation units (effect size) using a paired t-test. This effect size was selected as one that is larger than those of existing adult scales such as the CMTNS (0.13) and the CMTES-R (0.20) (36, 37).

A sample of 60 individuals with CMT1A subjects at baseline will provide > 80% power to detect correlations between muscle FF and clinical outcome variables as small as 0.35, using a two-tailed test and a 5% significance level. Anticipating a dropout of 15%, a sample size of 51 CMT1A subjects at 24 months will provide 90% power to detect significance of a mean change of 0.46 standard deviation (SD) units (absolute increase in FF of 0.69%) (23) using a paired t-test. Sample sizes of 51 CMT1A subjects and 21 controls will provide 80% power to detect a group difference in mean change of 0.65%, assuming standard deviations of 1.5% in the CMT1A group and 0.4% in controls (23), using a two-sample t-test. Lastly, for validating RCM of MC density as a sensory biomarker a sample size of 135 CMT1A subjects at baseline will provide >90% power to detect correlations between MC density and clinical outcome variables as small as 0.28. Again, it is anticipated that 115 participants will complete assessments at 30 months which will provide 90% power to detect significance of a mean change of 0.31 standard deviation units using a paired t-test (36).

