Longitudinal analyses will be performed to evaluate responsiveness to change over time of MRI quantified muscle FF in the 60 adults with CMT1A. MRI scans will be evaluated at baseline, 12 and 24 months. Effect sizes and standardized response means will be computed for muscle FF. MMRM analyses will be performed to model mean changes over time in these outcomes (41). We will explore possible predictors of change over time using these models by adding interaction terms between covariates (e.g., age, sex, baseline severity) and month to the models. Mean changes over time, with corresponding 95% confidence intervals and *p*-values, will be obtained from these models. The results may suggest targeted eligibility criteria in future studies that will identify subjects more likely to change over time and, hence, increase power. Change in FF will be correlated with changes in the above clinical and electrophysiologic outcomes in CMT1A subjects to provide longitudinal validation of the MRI biomarker. This will assess whether early changes in FF are associated with longer term functional outcomes.

Reliability of MC density at digit V and the thenar eminence in participants with CMT1A will be assessed using a sample of 20 RCM image sets and two reviewers. Intra-rater reliability will be quantified using intraclass correlation coefficients (ICCs), estimated using a one-way random effects analysis of variance model with participant treated as a random effect. Interrater reliability will be evaluated using ICCs estimated using a two-way random effects analysis of variance model with participant and rater treated as random effects. The ICCs should exceed 0.80; any lower values will motivate us to reevaluate the scoring process and/or perform further training of the raters.

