Baseline associations between MC densities and the touch sensation thresholds and FF of the calf muscle will be examined using correlation and regression analyses. Also at baseline, differences between CMT1A subjects and controls with respect to mean MC density will be evaluated using analysis of covariance models that include group as well as age, gender, hand dimension (if appropriate), and height. For longitudinal data, MMRM analyses will be performed to model mean changes over time in the MC density outcomes (41). We will explore possible predictors of change over time using these models by adding interaction terms between covariates (e.g., age, sex, baseline severity) and month to the models. Mean changes over time, with corresponding 95% confidence intervals and *p* values, will be obtained from these models. Changes in MC density will be correlated with changes in the COAs, touch sensation thresholds, ONLS and PROs in CMT1A subjects to provide longitudinal validation of this sensory biomarker.

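### A larger mean change in muscle fat fraction does not by itself increase power; the exploratory eligibility work should also report the SD of change and the SRM in each candidate subgroup

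*Protocol article*

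**What the plan says.** The Introduction closes with a secondary aim: "We also aim to increase the efficiency of trial design by using data to refine eligibility criteria". For FF, the longitudinal MRI paragraph under Statistical Considerations gives the route. Interactions between covariates (age, sex and baseline severity are the examples) and month are added to the MMRM. The models yield mean changes with 95% confidence intervals and p-values. The paragraph then says that the results may point to targeted criteria for later studies that will "identify subjects more likely to change over time and, hence, increase power".

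The same paragraph plans effect sizes and standardized response means (SRMs) for FF, without mentioning subgroups. The CMT-FOM paragraphs plan bootstrap comparison of SRMs, but between measures and not between kinds of participants.

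The Sample Size section itself works with a ratio. It powers the 24-month FF analysis on a "mean change of 0.46 standard deviation (SD) units (absolute increase in FF of 0.69" percent), and the two-group comparison "assuming standard deviations of 1.5% in the CMT1A group and 0.4% in controls".

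**The concern.** The word linking the two halves of the quoted sentence asserts that selecting people who change more raises power. An interaction with month shows how mean change differs by age, sex or severity. It does not show how variable the change is within each kind of participant, and that variability is the other half of the power calculation. If faster-changing participants are also more heterogeneous, a criterion suggested by mean change could leave a later trial needing as many patients as before, or more. It would also have narrowed recruitment in a disease that the Discussion calls rare.

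**Working it through.** **Inputs from the Sample Size section.** Mean 24-month FF change is 0.69%, stated as 0.46 SD units. The SD of change in CMT1A is 1.5%. The number at 24 months is 51 ("Anticipating a dropout of 15%, a sample size of 51 CMT1A subjects at 24 months"). The two-sided 5% level is stated for the FF correlation ("using a two-tailed test and a 5% significance level") and is assumed here to apply to the t-test as well.

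**1. Reproduce the plan's own figure.** 0.69/1.5 = 0.46. For a paired t-test with n = 51, the noncentrality is 0.46 × √51 = 3.29 on 50 degrees of freedom, which gives 89.6% power. The stated value is 90%, so it reproduces. It does so through the ratio of mean to SD, not through the mean alone.

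**2. Effect of a larger mean.** Required sample size is proportional to (SD/mean)², so relative to the whole cohort it is (SD ratio / mean ratio)². With an assumed mean ratio of 1.3:

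- SD unchanged: (1.0/1.3)² = 0.59
- SD 30% larger: (1.3/1.3)² = 1.00
- SD 50% larger: (1.5/1.3)² = 1.33

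**3. On the FF scale.** Assume a future two-arm trial in which treatment halves the mean change, with 80% power and a two-sided 5% level. Then n per arm = 2(1.960 + 0.842)² SD² / (0.5 × mean)². The first row uses the document's figures; the other means and SDs are assumptions.

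| Mean change | SD | SRM | n per arm | Paired power at n = 51 |
|---|---|---|---|---|
| 0.69 | 1.5 | 0.46 | 297 | 89.6% |
| 0.90 | 1.5 | 0.60 | 175 | 98.7% |
| 0.90 | 1.96 | 0.46 | 297 | 89.6% |
| 0.90 | 2.2 | 0.41 | 376 | 81.7% |
| 0.90 | 2.5 | 0.36 | 485 | 71.3% |

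Break-even is where the SD rises by the same factor as the mean: 0.90/0.69 = 1.30, that is, an SD of 0.90/0.46 = 1.96.

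**4. Is a reversal compatible with the stated overall figures?** Take two equal halves with assumed mean/SD of 0.80/1.90 and 0.58/0.93. The pooled mean is (0.80 + 0.58)/2 = 0.69. The pooled variance is (1.90² + 0.93²)/2 + 0.11² = 2.25, so the SD is 1.50. Both match the document. The faster half has SRM 0.42 and needs 355 per arm, against 297 unrestricted and 162 in the slower half. A different split goes the other way: a faster half with 1.0/1.9 (SRM 0.53) needs 227 against 297. Both outcomes fit the published overall mean and SD.

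**5. Precision of a subgroup SRM.** For half of the 51 completers, about 25 people, the approximate standard error at SRM 0.46 is √(1/25 + 0.46²/50) = 0.21. The 95% interval is then about ±0.41.

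**The case against.** The strongest reply is that the sentence fixes nothing. The analysis is described as exploratory, its results only may suggest criteria, and no threshold or ranking by mean change is stated. A reader might infer that the plan contains a rule selecting whoever changes most on average; it does not. How exploratory results become eligibility advice could also sit in a fuller document. Nothing in the article excludes weighing variability, and it already plans SRMs for FF overall.

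A second reply concerns the evidence. A reader might take the SDs of 1.5% and 0.4% as showing that spread grows with progression. They compare patients with healthy controls, not strata of CMT1A, so they say nothing about whether SD rises with mean change among eligible patients. They may even point the other way. The article also states that "Sample sizes of 51 CMT1A subjects and 21 controls will provide 80% power to detect a group difference in mean change of 0.65" percent. If that figure and 0.69% are both read as expected changes (an assumption, since 0.65% is given only as a detectable difference), control change is about 0.04% and its SRM 0.04/0.4 = 0.1, well below 0.46 in CMT1A.

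Third, the subgroup magnitudes are invented, and with about 25 people per half a strict requirement that a criterion raise the SRM could rarely be decided.

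These replies stand as limits on the size of the point and on the form of the remedy. They do not rescue the stated inference: the article itself moves from greater likelihood of change to greater power, and that step needs a condition it does not give.

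**Conclusion.** The point holds as a qualification of one stated inference. A larger mean FF change increases power only if the SD of change rises by a smaller factor, and the interaction on mean change cannot show whether it does. The size is unknown because the document gives no subgroup means or SDs. Under the assumptions shown, the relative sample size runs from 0.59 to 1.33 for a 30% larger mean. Reading the SRM as a guide to a later trial's power also assumes that treatment slows progression proportionally.

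A reader might go further and conclude that enrichment here would lower power; the documents do not show that, and some splits consistent with their figures give a gain. No stated number is wrong, and this study's own design and sample size are unaffected. The point is confined to the FF paragraph and the secondary aim in the Introduction. The Meissner corpuscle paragraph uses the same kind of interaction ("Mean changes over time, with corresponding 95% confidence intervals and *p* values, will be obtained from these models") but draws no conclusion about eligibility or power.

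**What to change.** For each candidate criterion explored for FF, report alongside the mean change:

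- the SD of change and the SRM in the eligible subgroup, with a bootstrap interval (or let the MMRM residual variance differ by subgroup);
- the implied sample size relative to the whole cohort, with the proportional-slowing assumption stated;
- the fraction of the cohort that remains eligible.

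Reword the sentence so that a gain in power is conditional on a higher SRM in the eligible subgroup than in the whole cohort. Present the results as exploratory, not as a pass/fail rule, because the intervals will seldom settle the question.

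The cost is a little more analysis on data already being collected, extending the bootstrap already planned for comparing SRMs between measures. The downside is wide intervals with about 51 MRI completers, so some criteria that look attractive on mean change will remain unresolved.

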### *In vivo* Reflectance Confocal Microscopy of Meissner's Corpuscles

*In vivo* RCM of MC has been identified as a novel approach to measure sensory neuropathy (25, 26, 28). MC density of the fingertip of digit V was found to be lower than that of healthy controls and was associated with overall CMT disease severity. In this study, a portable *in vivo* confocal reflectance microscope (Vivascope 3000, Caliber Imaging and Diagnostics Inc.) will be used to assess MC density. *In vivo* RCM of MCs will be performed on the palmar surface of the distal phalanx of digit V and the thenar eminence of the hand. The non-dominant side will be used, unless there is a history of focal trauma, or entrapment neuropathy, that will confound or preclude imaging. In that instance, RCM and touch pressure sensation threshold testing will be done on the dominant side. The *in-vivo* RCM procedure involves applying a few drops of bio-compatible index matching fluid to the skin site, touching the window of the lens to the surface of the skin and obtaining a standardized set of images using the system's operating software (Figure 3).

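### The planned ICCs for Meissner corpuscle density cover reading error only, so they cannot by themselves meet the aim of reliability for multi-site use

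*Protocol article*

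**What the plan says.** The final paragraph of the Introduction lists reliability among the properties to be assessed for reflectance confocal microscopy (RCM) of MC density, so that it can serve as a "sensory disease progression biomarker for use in multi-site CMT1A trials".

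The method is under Statistical Considerations, in the text that follows the heading Validation of the CMT-FOM. Reliability at digit V and the thenar eminence "will be assessed using a sample of 20 RCM image sets and two reviewers". The intra-rater ICC is "estimated using a one-way random effects analysis of variance model with participant treated as a random effect". The inter-rater ICC comes from a "two-way random effects analysis of variance model with participant and rater treated as random effects". The criterion and its consequence are: "The ICCs should exceed 0.80; any lower values will motivate us to reevaluate the scoring process and/or perform further training of the raters".

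The section on RCM describes acquisition as "touching the window of the lens to the surface of the skin and obtaining a standardized set of images". Images are taken at the sites and counted centrally and blinded (Study Description). Training and Quality Assurance adds that some site staff were trained by peers and remotely, with live feedback from the reading centre, and that uploaded image sets are checked for quality. Table 1 schedules RCM at every assessment visit, including baseline and 6 months, and lists no repeat session.

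**The concern.** An ICC describes only the sources of variation that differ between its replicates. Here the replicates are readings, and the random terms are participant and, in one of the two models, rater. When a participant returns, the lens is placed again, a slightly different patch of skin is imaged, and the operator may have changed. None of this enters either ICC, and the stated remedy for a low value is likewise confined to scoring and raters.

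The article treats its other main measures differently. For MRI it describes inter-scan reproducibility approved at each site (Training and Quality Assurance) and test-retest images two weeks apart (Figure 2 caption). For the CMT-FOM it cites test-retest reliability from the initial study. RCM has no counterpart.

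Two things are at stake. If MC density changes little over 30 months, reader ICCs cannot show whether the biology is slow or the imaging is noisy. And a detectable change for one participant derived from the reader ICC would be too small.

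**Working it through.** **1. The plan's own figures (Sample Size).** The 0.80 criterion and the 20 image sets have no stated derivation, so the power figures are what can be reproduced.

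- Paired t-test, n = 115, mean change 0.31 SD, two-sided 5% (stated for the MRI correlations, assumed here): noncentrality 0.31 × √115 = 3.32 on 114 df, power 0.909. The plan states 90%.
- Correlation 0.28, n = 135, Fisher z: 0.288 × √132 − 1.96 = 1.35, power 0.911. The plan states more than 90%.
- 135 × 0.85 = 114.75, or about 115 completers.

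These hold. The 0.31 is in units of the SD of change, which already includes acquisition and reading error.

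**2. What the reader ICC leaves out.** Set between-participant variance to 1 and re-imaging variance to q times that. Acquisition reliability is 1/(1 + q). Reader variance on a given image is (1 + q)(1/ICC_reader − 1). Then

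ICC_total = 1 / [(1 + q) + (1 + q)(1/ICC_reader − 1)] = ICC_reader × 1/(1 + q).

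The document gives no value for q, so a range is assumed:

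| Reader ICC | q = 0 | q = 0.10 | q = 0.25 | q = 0.50 | q = 1.0 |
|---|---|---|---|---|---|
| 0.80 | 0.80 | 0.73 | 0.64 | 0.53 | 0.40 |
| 0.90 | 0.90 | 0.82 | 0.72 | 0.60 | 0.45 |
| 0.95 | 0.95 | 0.86 | 0.76 | 0.63 | 0.48 |

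The reader ICC equals the visit-to-visit ICC only if q = 0.

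**3. Change detectable in one participant.** In units of the baseline SD, MDC95 = 1.96 × √[2(1 − ICC)].

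- Reading error only, ICC 0.90: 1.96 × √0.20 = 0.88 SD.
- Acquisition reliability 0.90 (assumed): total ICC 0.90 × 0.90 = 0.81, and 1.96 × √0.38 = 1.21 SD.
- Acquisition reliability 0.70 (assumed): total ICC 0.90 × 0.70 = 0.63, and 1.96 × √0.74 = 1.69 SD.

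**4. Precision of the reader ICC (a side point).** One-way model, 20 sets, two readings, observed ICC 0.80: F = 1.8/0.2 = 9. Dividing by 2.48 and multiplying by 2.51 (97.5% F points on 19, 20 and 20, 19 df) gives 3.63 and 22.6. Applying (F − 1)/(F + 1) gives a 95% CI of 0.57 to 0.92.

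**5. What the scheduled data can give.** With d the change from baseline to 6 months, the within-person SD after removing mean change is SD(d)/√2. MDC95 is 1.96 × √2 × SD(d)/√2 = 1.96 × SD(d). The 6-month standardized response mean already needs SD(d).

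**The case against.** The strongest reply is that acquisition error is not lost. The standardized response means planned for the biomarkers at each time point divide by the observed SD of change, and the repeated-measures models use the same repeated acquisitions. A future trial would be sized from these, not from a reader ICC. This stands. A reader might infer that the power statement or the responsiveness analyses are wrong; they are not.

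It is also fair that the ICCs are already called intra-rater and inter-rater, that the remedy fits a check of the reading core, and that the article nowhere says that passing 0.80 validates the biomarker. Validation also rests on group differences, convergent associations and longitudinal change. What remains is that these ICCs are the whole of what the plan offers under reliability of MC density, against an aim that is wider.

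Site training with live feedback and image-quality review will limit acquisition error, but they do not measure it. The abstract says that initial studies found the measures reliable, and earlier RCM work is cited. The article reports no RCM retest result, so whether one exists cannot be settled from it. It also does not literally say that the same stored sets are scored again; that is the natural reading of the sample, the models and the remedy.

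Finally, one might want to move the 0.80 rule to a 6-month ICC. That goes too far. Differences between participants in true progression would count as error, so a failure could not be attributed to the imaging.

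**Conclusion.** The point holds in a limited form. The stated reliability analysis answers whether the reading core scores images consistently. It does not answer whether MC density is reproducible when a participant is imaged again or by another operator, nor how sites compare, so by itself it does not meet the article's reliability aim for multi-site use.

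The size of the gap is unknown. The total ICC of 0.63 to 0.81 and the MDC95 of 1.7 to 1.2 SD rest on an assumed reader ICC of 0.90 and an assumed acquisition reliability of 0.70 to 0.90. They show how far a reader ICC can depart from total reliability. A reader might infer that MC density is unreliable; nothing in the document shows that.

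Condensation into an article does not explain the gap away, because the RCM reliability design is given down to its variance models. No planned test fails. A stated aim is only partly served, and data already scheduled can largely fill the gap.

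**What to change.** - Keep the reader ICCs and the 0.80 rule as a check of the reading core, and state that they show reader reliability only.
- Add, from the baseline and 6-month RCM data (135 participants at baseline; those with both visits contribute), the within-person SD after removing mean change, the visit-to-visit ICC and the 95% minimal detectable change. Give each with a confidence interval, for digit V and the thenar eminence.
- Show by-site results as descriptive only. If all five enrolling sites contributed equally there would be 135/5 = 27 participants per site, too few for precise site ICCs. If each participant is imaged at one site throughout, a constant offset between sites is not in the within-person SD, and the text should say so.
- Present these figures as a conservative bound on reliability, with no pass/fail threshold, because 6-month differences in true progression count as error.

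The cost is analysis-plan wording and a few derived quantities, with no extra imaging or reading. The downside is small: the reported reliability will probably look less favourable than the reader ICCs alone.

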## Discussion

While CMT1A is the most common type of CMT, accounting for over 50 percent of cases, it is still a rare condition. CMT1A is slowly progressive; as such, it has proven challenging to measure disease progression with existing CMT outcome measures in the context of clinical trials. Multi-site studies are necessary to recruit sample sizes large enough to validate outcome measures and inform future clinical trial needs. The ACT-CMT study, has been designed to address these needs and prepare for future clinical trials in CMT1A. The eligibility criteria were selected to reflect the potential criteria for trials involving adults with CMT1A; however, the data from this study will likely be able to be leveraged to optimize eligibility criteria.

The CMT-FOM is hypothesized to be a unidimensional measure that with the CMTInfS and CMTPedS will provide whole of life CMT functional outcome measures. Initial studies have documented the reliability and supported the validity of this COA; however, this study will provide the sample size necessary for full validation, Rasch analysis, and examination of the ability of the CMT-FOM to detect disease progression over a time period that is feasible for the conduct of multi-center trials. The ACT-CMT protocol will also promote rigorous validation of existing COAs that have been used in prior trials in CMT (including the CMTES and the ONLS) for comparison with the CMT-FOM. Moreover, we have recently developed and reported cross-sectional validation of a disease specific patient reported outcome measure (CMT-HI) to capture patient reported disease burden in CMT (34). The ACT-CMT protocol will permit careful longitudinal validation of the responsiveness to change of the CMT-HI. Insight into clinically meaningful change in outcome measures for hereditary neuropathies is lacking. The current protocol will rigorously assess the clinically meaningful change of each COA.

Validated biomarkers of the motor and sensory components of CMT1A for multicenter trial application has been identified as a gap in clinical trial readiness. Given the slow progression of CMT1A, biomarkers that have capacity to demonstrate slowing of disease progression or improvement, prior to changes in physical functioning, neurologic impairment or symptoms, will enable go/no go decisions in early phase clinical trials in CMT1A. Indeed, data to date for lower extremity MRI of muscle FF, has suggested that this motor biomarker is highly responsive to change (standardized response mean >0.8) in CMT1A. The ACT-CMT protocol will establish the sensitivity to change of MRI of intramuscular FF and RCM of MC density. ACT-CMT will also determine whether these biomarkers can be implemented at multiple centers, and in the case of MRI, using MRI scanners from different manufacturers. This protocol will provide the data to determine whether changes in calf intramuscular FF and RCM of MC density predict changes on clinician administered and patient reported outcome measures in CMT1A. These data will support the implementation of these biomarkers in future trials in CMT1A.

Successful conduct of multicenter, transcontinental clinical trials in rare disorders such as CMT1A require the establishment of robust clinical trial site capacity, site training and certification in the administration of COAs and imaging, and data transfer procedures that meet data privacy standards. Moreover, efficient and reliable central image analysis cores are required for modalities such as MRI of IMFA and quantitation of RCM of MC densities. The ACT-CMT study will establish the multicenter capacity, expertise and quality assurance to allow for seamless transition from the clinical trial readiness study to implementation of clinical trials in CMT1A. The data that will emerge from this study will inform participant selection criteria, outcome measure and biomarker selection, sample size and trial duration considerations. These data will be made available to the scientific community and will inform discussions with regulatory agencies during early stages of drug development. Additionally, the ACT-CMT study will establish a large cohort of adults with well characterized CMT1A, which will accelerate recruitment for future therapeutic trials in CMT1A, and elucidate the natural history of CMT1A in unprecedented detail using a range of clinician administered and patient reported outcome assessments and biomarkers, supporting clinical trial design.

The ACT-CMT study has some potential limitations. This study is being conducted at sites in the United States, UK and Italy. The clinician administered and patient reported outcome measures are currently established for English and Italian speaking study personnel and participants. If validated, these COAs will need to be extended to other languages for utility in global clinical trials. The ACT-CMT protocol focuses on individuals 18–75 years of age, as the majority of individuals with symptomatic CMT1A are adults, and critical gaps exist in outcome measures for adults with CMT1A. However, as therapeutic effects will potentially be greatest with intervention prior to development of significant disability, early treatment in late childhood or adolescence will be critical for CMT1A. The CMTPedS, on which the CMT-FOM is modeled, has already been longitudinally validated for children and adolescents with CMT1A, and studies are proceeding in parallel with ACT-CMT through the INC to evaluate biomarkers. Additionally, the use of MRI of calf and foot muscle to evaluate FF in children with CMT1A is being examined at two of the ACT-CMT sites (London and Iowa). Therefore, the findings of ACT-CMT will need to be considered in conjunction with data emerging from these studies in children when planning future clinical trial programs in CMT1A.

We anticipate that the ACT-CMT study will fill critical gaps in the toolkit of outcome measures for early and late stage clinical trials in CMT1A and accelerate the pathway toward design of successful clinical trials. CMT1A has overlapping clinical features with other major forms of CMT including CMT1B, CMTX1 and other forms. The outcome assessments and motor and sensory biomarkers incorporated in the ACT-CMT study will likely meet the needs of clinical trials for other forms of CMT. This study, therefore, creates a framework that can be used to validate these and other measures in preparation for clinical trials in other subtypes of CMT.

